### Study objectives

2.1

The main objective of this study is to address whether the introduction of the ReMindCare App into daily clinical practice improves the quality of treatment for patients in a first episode of psychosis programme (FEPP).

Specifically, the aims of the study are (1) to assess the effectiveness of the ReMindCare app, in terms of improvement of adherence to anti‐psychotic medication, early detection of relapses and improvement of communication with clinicians, vs treatment as usual in patients with a psychotic disorder; (2) to analyse the use of the ReMindCare app by the patients in terms of rates of adherence, compliance, alerts generated and the total time using the app; and (3) to assess the satisfaction of patients with using the app and the perceived usability of the ReMindCare app.

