#### Discontinuation and withdrawal

2.4.3

A patient's participation in the study will be discontinued if:The patient provides an explicit notification of not wishing to continue using the app.Lack of use the app for a period longer than 2 months after having been contacted by the research group over that period of inactivity.Discharged from the FEPP or if their consent is revoked.Given the naturalistic nature of this study, in case of discontinuation or withdrawal, patients will continue with the usual psychiatric treatment at the hospital.

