Baseline surveys, including clinical and sociodemographic information and clinical standardized questionnaires, were administered before the enrolment of the patient in the study. As shown in Table 1, data regarding the main outcomes, such as adherence to medication, number of relapses, number of visits to the hospital urgent care units and number of hospital admissions, will be collected and analysed at the end of the first, second and fifth years of the intervention. Moreover, information generated for patients through the use of the app will also be analysed at the same timepoints. Finally, to analyse the feedback of patients regarding the use of the app, we plan to conduct focus groups at the end of the first year of the intervention, and we have also designed a “satisfaction questionnaire” (SQ) that patients will complete at the end of the first year of the intervention or before discontinuing the use of the app (if discontinuation occurs before the first year of app usage). This SQ was made for the purpose of this research study and is based on previous satisfaction and usability questionnaires, such as the user version of the Mobile Application Rating Scale (uMARS) (Stoyanov, Hides, Kavanagh, & Wilson, 2016), the System Usability Scale (SUS) (Brooke, 1996), EnLight: a tool for mobile and web‐based eHealth interventions (Baumel, Faber, Mathur, Kane, & Muench, 2017) and the App Quality Evaluation (AQEL) (DiFilippo, Huang, & Chapman‐Novakofski, 2017). This questionnaire is displayed in Appendix B.

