### Planned data analysis

2.7

Descriptive analyses of sociodemographic and clinical variables will be conducted. A multivariate data analysis will be carried out to explore relationships between sociodemographic and clinical variables and adherence to treatment and ReMindCare measures. An ANOVA model of repeated measures will be used for the main research outcomes. All analyses will be conducted with an alpha set at *P* < 0.05.

These preliminary quantitative data analyses and the preliminary results regarding patient compliance, retention rate and perceived satisfaction with the use of the ReMindCare app are expected by the end of the first year of using the app (March 2020). At that time, qualitative analyses of data are also planned.

Subsequent analysis of the data will be conducted at the end of the second and fifth years of use of the app.

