### Anticipated results

4.1

On the basis of previous studies (Bonet et al., 2017; Firth et al., 2016; Gitlow et al., 2017) that confirmed the interest of patients with psychosis in e‐health interventions and based on the high interest in owning an e‐health app that we found in our survey study (Bonet et al., 2018), we expect an acceptable retention rate (beyond 70%).

Moreover, based on previous studies (Ben‐Zeev et al., 2014; Ben‐Zeev, Kaiser, & Krzos, 2014; Brenner & Ben‐Zeev, 2014; Kimhy, Vakhrusheva, Liu, & Wang, 2014; Macias et al., 2015) that found rates of response to the communications of e‐health apps to be higher than 70%, we also expect moderate compliance with the app's communications (beyond 70%).

Furthermore, as previous studies have stated that electronic assessments are valid and reliable measures (Brenner & Ben‐Zeev, 2014; Kimhy et al., 2014; Palmier‐Claus et al., 2013; Spaniel et al., 2008), and based on preliminary perceptions obtained from the first 7 months of the current intervention, we expect that the use of the ReMindCare app would produce the following differences in the treatment of psychotic disorders:
*Improved quality of treatment delivery for clinicians*: Graphics of daily and weekly questionnaires allow clinicians to rapidly assess the status of the patient and to specifically orient their interactions with the patient to problematic areas. An improvement in the quality of evaluation is also expected. Perceptions of the clinicians regarding these issues will be qualitatively assessed in focus groups.
*Improved insight about the illness and mental health status for patients*: Sharing with patients their responses to the app is expected to increase accuracy of information and to decrease bias in this process. Moreover, it is expected that, by discussing their app responses with the patients, insight about their illness and their health status will increase. These perceptions will be mainly assessed by the “satisfaction questionnaire” (SQ), and they will also be assessed qualitatively in focus groups. Moreover, changes in insight between baseline and 1 year of intervention will be assessed by using the BCIS (Beck et al., 2004).

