*Improved quality of communication between patient and clinician*: It is expected that patients will feel more understood as a result of improvements in evaluation and quality of their interactions with the clinician, which could lead to an enhancement of the overall quality of communication and alliance between patient and clinician. Again, this will be assessed by the SQ and the focus groups.
*Improved adherence to treatment for patients*: As a result of improvements in insight about the illness and improvements in alliance with clinicians, an enhancement of adherence to treatment is also anticipated. Significant differences are expected in the SMAQ (Hogan et al., 1983) scores of patients between baseline and 1 year of intervention. Moreover, the number of relapses, treatment dropouts and rates of compliance and adherence to ReMindCare tests will also be analysed in this regard. It is expected that the more patients use ReMindCare (high rates of engagement and compliance), the fewer treatment dropouts and relapses there will be.
*Improved early relapse detection and hospital admission reduction*: Again, higher rates of engagement with ReMindCare are expected to produce lower hospital admissions, early detection of relapses and fewer visits to urgent care units. Moreover, rates of relapses, changes in medication and visits to urgent care units will be compared among patients who used the “urgent consultation” function and those who do not. We expect that using this function will improve the quality of early detection.
*Improved quality of communication between health care providers and improved quality of treatment decisions*: Due to general access of health care professionals to ReMindCare reports on the EMR, we expect improved communication between health professionals and, because of this, improved quality of treatment. Perceptions of clinicians on this issue will be qualitatively assessed in focus groups.

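### The repeated-measures ANOVA named for the main outcomes discards adherence scores already recorded from patients who later stop; a mixed model would keep them

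*Protocol article*

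**What the plan says.** All references are to the protocol article.

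- **Model.** Section 2.7 (Planned data analysis): "An ANOVA model of repeated measures will be used for the main research outcomes". The section names no mixed model, imputation or other way of handling incomplete patients.
- **Schedule.** Section 2.6 says that the main outcomes, adherence among them, "will be collected and analysed at the end of the first, second and fifth years of the intervention". Table 1 adds a baseline SMAQ. A full record is therefore two scores at the year-1 analysis, three at year 2 and four at year 5. Section 2.7 confirms the later looks: "Subsequent analysis of the data will be conducted at the end of the second and fifth years of use of the app".
- **Leaving.** Under section 2.4.3 a patient's "participation in the study will be discontinued if" the patient asks to stop, stays inactive for more than 2 months after being contacted, is discharged from the programme or revokes consent. For patients who stop before year 1, section 2.6 foresees only the satisfaction questionnaire.
- **Expected retention.** Section 4.1: "we expect an acceptable retention rate (beyond 70" (per cent). No period is attached.
- **Engagement and outcome.** Section 4.1, under adherence: "It is expected that the more patients use ReMindCare (high rates of engagement and compliance), the fewer treatment dropouts and relapses there will be".
- **Aim.** Section 2.1: "to assess the effectiveness of the ReMindCare app, in terms of improvement of adherence to anti‐psychotic medication", in patients with a psychotic disorder.

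**The concern.** The named model, as classically run, works on complete rows. A patient with baseline and year-1 scores but no year-2 score contributes nothing to the year-2 analysis. A patient with three of four scores contributes nothing at year 5. At year 1, a patient who leaves early loses the baseline score.

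Two things are at stake. One is precision in a small cohort, because data already collected go unused. The other is what the result means. The aim is about patients given the app, whereas the analysis would describe those who stayed to the last assessment. Complete-case analysis is safe only if leaving is unrelated to adherence, and the article itself expects engagement to go with outcome.

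**Working it through.** The article gives no sample size, power or missing-data figure for this point, so there is nothing to reproduce. Three checks were made.

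**1. Does the method need complete rows?** A standard repeated-measures ANOVA routine was run on 57 simulated patients with three time points, 17 of them lacking the last. It refused the data as unbalanced. Incomplete patients must be removed before it will run.

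**2. How many recorded scores are lost?** Inputs: N = 57 (section 3, enrolled so far) and annual retention r, which is assumed because the 70% has no period. Patients seen at years 0, 1, 2 and 5 are N, Nr, Nr² and Nr⁵. Discarded scores = recorded scores minus (number of time points × completers).

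For r = 0.7 at year 2, recorded = 57 + 39.9 + 27.9 = 125 and used = 3 × 27.9 = 84. The loss is 41 of 125 = 33%. At year 5, recorded = 125 + 9.6 = 134 and used = 4 × 9.6 = 38. The loss is 96 of 134 = 71%.

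| Annual retention | Patients at years 1 / 2 / 5 | Discarded, year-2 analysis | Discarded, year-5 analysis |
|---|---|---|---|
| 90% | 51 / 46 / 34 | 16 of 154 (10%) | 53 of 188 (28%) |
| 80% | 46 / 36 / 19 | 30 of 139 (21%) | 83 of 158 (53%) |
| 70% | 40 / 28 / 10 | 41 of 125 (33%) | 96 of 134 (71%) |

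If 70% is instead the total retained to the final analysis, with even loss:

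- Year 2: 57 + 48.4 + 39.9 = 145 recorded, 3 × 39.9 = 120 used, about 26 lost (18%).
- Year 5: 57 + 53.6 + 50.2 + 39.9 = 201 recorded, 4 × 39.9 = 160 used, 41 lost (20%).

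These counts need no assumption about why patients leave.

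**3. Is the estimated change biased, and which way?** Large-sample simulation of the year-2 analysis with no true change, SD 1 and higher scores better. Assumptions: equal correlation 0.5 or 0.7 between times, and log-odds of staying rising by 1 per SD of the last recorded score. Complete-case change from baseline, in SD:

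| When patients leave | Correlation | To year 1 | To year 2 |
|---|---|---|---|
| None before year 1, 30% between years 1 and 2 | 0.5 | +0.13 | 0.00 |
| Same | 0.7 | +0.08 | 0.00 |
| 30% in total, same rate in both years | 0.5 | 0.00 | -0.07 |
| Same | 0.7 | 0.00 | -0.04 |
| 30% in each year | 0.5 | +0.01 | -0.12 |
| Same | 0.7 | +0.01 | -0.07 |
| 30% before year 1, then 10% | 0.5 | -0.08 | -0.12 |
| Same | 0.7 | -0.05 | -0.07 |

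Likelihood-type means using every recorded score gave changes within 0.003 SD of zero in every row.

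In a four-time simulation of the year-5 analysis (70% annual retention, correlation 0.5), completers' means were 0.59, 0.59, 0.76 and 0.48, where the truth is 0. The change to year 2 is 0.76 - 0.59 = +0.17 and the change to year 5 is 0.48 - 0.59 = -0.11. The sign can differ between contrasts within one analysis.

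On precision, 400 replicates with n = 57 in the first row's setting gave an empirical SD of the year-1 change of 0.161 with complete cases and 0.136 with all scores: 0.161 / 0.136 = 1.18, or 18% larger.

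**The case against.** - **The article never says that incomplete patients are dropped.** True. Complete-case use follows from the named method, and a fuller analysis plan might add imputation or a mixed model. But the article fixes the model, and such a plan would have to replace or supplement it. The point concerns a stated choice, not missing detail.
- **The stated SMAQ hypothesis is safe.** Section 4.1 expects a difference between baseline and 1 year. At the year-1 analysis, everyone with both scores is included whatever happens later. This stands as far as it goes. The baseline scores of those who left before year 1 are still dropped there, and the years 2 and 5 analyses lose much more.
- **A reader might infer that dropping leavers inflates the apparent improvement.** The documents do not support a direction. The +0.13 SD at year 1 requires that nobody leaves before year 1, whereas section 2.6 expressly provides for earlier exits. With earlier exits the year-1 change is close to zero or negative and the year-2 change is understated.
- **The link between leaving and outcome is stretched.** The article speaks of dropout from treatment, which is not the same as stopping the app. Its expectation makes completely random loss doubtful but does not establish a mechanism. The simulated dropout slope is an assumption.
- **The simulations are single-group.** Section 4.2 also plans a comparison with age-matched controls. The effect on that contrast was not assessed.

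**Conclusion.** The concern holds as a matter of discarded data, lost precision and a result confined to completers. At 57 patients the year-2 analysis loses about 10 to 33% of recorded SMAQ scores and the year-5 analysis about 20 to 71%, over annual retention of 70 to 90% and the alternative reading of 70% as the total. At 70% a year, only about 10 patients remain in the year-5 ANOVA.

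Bias in the change from baseline is possible, but its sign is not settled. In the year-2 analysis it ran from about -0.12 to +0.13 SD, depending on when patients leave, with correlation 0.5 to 0.7 and a dropout log-odds of 1 per SD assumed. No general claim of overstatement is warranted. The change is worth making because a better method costs almost nothing; the point does not show that the planned result would be wrong.

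**What to change.** In section 2.7, name a likelihood-based mixed model for repeated measures for the SMAQ. Time should be categorical and the covariance unstructured where it can be estimated. If the SMAQ is analysed in categories or as adherent yes/no, use an ordinal or logistic mixed model. Include every enrolled patient with at least one SMAQ score, keep all recorded scores, and say that the estimate refers to all enrolled users. Report the complete-case ANOVA as a sensitivity analysis.

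Cost: a sentence or two in the analysis section and slightly more analysis work, with no new patients or data. Downside: the model relies on missing at random. That is weaker than what the complete-case ANOVA needs, but it does not repair bias from outcomes that go unrecorded after a patient stops. With about 10 patients at year 5, the unstructured covariance may not be estimable, so a simpler structure should be named in advance as the fallback.

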However, some limitations must be taken into consideration. First, because of the characteristics of this real‐world intervention, our study is not randomized or controlled. However, we plan to compare the main outcomes of the use of the app between users and age‐matched controls, although the groups may differ in some characteristics. Another limitation is that ReMindCare has only been designed for Android systems, although an iOS version of the app is being designed.

To our knowledge, this is one of the earliest e‐health interventions for patients with psychosis implemented as a standard care tool integrated into clinical practice in the public hospital workflow. Real‐time health information is being collected and used to work together with patients to improve the quality of real‐world health care delivery.

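### Four unranked main outcomes are each tested at 0.05 at years 1, 2 and 5 with no primary outcome or time point, so the chance of some false significant result is well above 5%

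*Protocol article*

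**What the plan says.** The Protocol article's Data collection and measures section lists "main outcomes, such as adherence to medication, number of relapses, number of visits to the hospital urgent care units and number of hospital admissions". None is placed above the others, and the wording leaves the list open. The same section states that these data "will be collected and analysed at the end of the first, second and fifth years of the intervention".

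Planned data analysis gives the method, "An ANOVA model of repeated measures will be used for the main research outcomes", and then the threshold: "All analyses will be conducted with an alpha set at" P < 0.05. It calls the first-year results preliminary and adds: "Subsequent analysis of the data will be conducted at the end of the second and fifth years of use of the app".

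Two other statements bear on the point. Under Anticipated results, "Significant differences are expected in the SMAQ" refers to scores between baseline and one year; it is an expectation, and SMAQ is not labelled primary. Under Strengths and limitations, the authors write "we plan to compare the main outcomes of the use of the app between users and" age-matched controls. That matches aim 1 in Study objectives, which sets the app against treatment as usual.

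**The concern.** Study objectives frames one main question: whether bringing the app into practice raises treatment quality. Four outcomes can answer it, at three times, each with its own 5% allowance. The plan does not say which outcome or which analysis settles the question. A significant result on any of them could therefore be presented as the answer, and the headline outcome could be chosen after the data are seen.

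The study is neither randomised nor controlled by design, so a chance finding has little else to hold it in check. The article also does more than leave error control to a later document: it fixes 0.05 for all analyses, and following that sentence as written produces the inflation.

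**Working it through.** **Inputs from the Protocol article**
- Per-test alpha: 0.05 (Planned data analysis).
- Main outcomes: 4; analyses: 3 (Data collection and measures).
- Test: repeated-measures ANOVA. Its F test is non-directional, so it is treated as two-sided.

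**Assumptions (not in the document)**
- One test per outcome per analysis, giving 4 × 3 = 12.
- Correlation between outcomes of 0 to 0.7.
- Dependence between analyses of two kinds: data accumulating on the same patients, with information proportional to 1, 2 and 5 years (correlations √(1/2) = 0.71, √(1/5) = 0.45, √(2/5) = 0.63), or a constant correlation of 0.7.
- A significant result on any main outcome counts as support for the main objective.

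The article states no family-wise error rate, so it has no figure of its own to reproduce beyond 0.05.

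**Independent tests**
- Either direction: 1 − 0.95^4 = 18.5%; 1 − 0.95^12 = 46.0%.
- Favourable direction only (0.025 per test): 1 − 0.975^4 = 9.6%; 1 − 0.975^12 = 26.2%.

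**Correlated tests** (simulated multivariate normal statistics, |Z| > 1.96 for either direction, Z > 1.96 for favourable)

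| Between-outcome correlation | One analysis, either direction | One analysis, favourable | Three analyses, cumulative data, either direction | Three analyses, cumulative data, favourable |
|---|---|---|---|---|
| 0 | 18.5% | 9.6% | 39% | 21.5% |
| 0.3 | 17.4% | 8.7% | 37% | 19% |
| 0.5 | 15.6% | 7.8% | 33% | 17% |
| 0.7 | 13.0% | 6.5% | 28% | 14% |

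A constant between-time correlation of 0.7, with between-outcome correlation 0.7, gives 27% in either direction and 13% in the favourable one. These are the lower ends of the quoted ranges. A between-outcome correlation of 0.8 would lower them a little further, to 11.4% per analysis and 24 to 25% overall (either direction).

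**After adjustment**
- One primary outcome at one time: 5%.
- Bonferroni at 0.05/4 = 0.0125 within one analysis: 1 − 0.9875^4 = 4.9% if independent, and never above 5%. Holm's method keeps the same 5% bound with more power.

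**Power cost** (paired t-test, assumed standardised effect 0.4, two-sided)

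| Complete pairs | 0.05 | 0.0167 (= 0.05/3) | 0.0125 (= 0.05/4) |
|---|---|---|---|
| 57 | 84% | 71% | 67% |
| 40 | 69% | 52% | 47% |

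The 57 is enrolment so far (Results); 40 is about 70% of it (0.70 × 57 = 39.9), the retention level that Anticipated results hopes to exceed.

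**The case against.** **A per-test alpha is not a decision rule.** The article never says that one significant outcome is enough, and multiplicity is often left to an analysis plan that is not shown here. The first part stands, so the error rates are conditional on that reading. The second does not remove the point: the article itself sets 0.05 for all analyses, and it leaves the main outcomes unranked against a single main objective.

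**Twelve tests is an assumed count.** A repeated-measures ANOVA could give one overall time test per outcome, and the year-1 results are called preliminary. This is fair. The four-test, per-analysis figure survives it. The preliminary label does not settle the matter, because the same threshold applies and no later analysis is named as confirmatory. The control comparison and the comparison of urgent-consultation users with non-users would add tests that are not counted here.

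**Stronger readings a reader might infer**
- That 13 to 19% and 27 to 46% are chances of a false improvement. They are not: they include false worsening, and the favourable figures are about half.
- That 46% is the rate to expect. It treats repeat analyses of the same patients as independent; with cumulative data the upper figure is about 39%.
- That the multivariate exploration adds a countable set of separate tests, with a predictable number of false positives. It is described as multivariate and exploratory, and several Table 1 entries are not single variables, so no count can be derived.
- That baseline-to-year-1 SMAQ is already the implied primary. It is an anticipated result and an uncontrolled before-after change, which alone cannot answer an aim set against treatment as usual.

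**Conclusion.** The point holds in a limited form. As written, the rule lets the main objective be supported by any of four equal outcomes at any of three times, each at 0.05. On that reading:
- at least one false significant result: about 13 to 19% per analysis, and about 27 to 39% over three analyses of the same patients (46% only if all 12 tests were independent);
- in the favourable direction: about 7 to 10% per analysis and 13 to 21% overall (26% if independent), against a nominal 2.5% for one test.

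The ranges rest on assumed correlations and on one test per outcome per analysis. The qualitative conclusion does not depend on their exact values. This should be corrected, but it does not invalidate the study.

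**What to change.** In Planned data analysis, before the first analysis:
1. Either apply Holm's adjustment across the four main outcomes at each analysis, or name one outcome, time point and comparison as primary at 0.05, with Holm for the other three. A primary should fit aim 1 and the age-matched control comparison; SMAQ is the natural candidate outcome.
2. State whether the year-1 preliminary analysis or a later one carries the main conclusion. Without this, Holm at each of three analyses bounds the overall error only at 3 × 5% = 15%.
3. Report the other time points, the multivariate exploration and the urgent-consultation comparison as exploratory estimates with 95% confidence intervals.

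No new data are needed. The cost is a stricter threshold for the smallest P value: 0.0125 over four outcomes or 0.0167 over three. At the assumed effect of 0.4, power for that outcome falls from 84% to 67–71% with 57 complete pairs, or from 69% to 47–52% with 40. A named primary keeps its full 0.05. These power figures are only a guide: three of the outcomes are counts, for which a paired t-test is a rough stand-in, and 57 is enrolment to date with recruitment still open, not a planned sample size.
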